#### **4.4 Early Withdrawal of Subjects**

##### **4.4.1 When and How to Withdraw Subjects**

The PI may withdraw a subject if he believes that for safety reasons it is in the best interest of the subject to be withdrawn. Please refer to section 8.5 (Stopping Rules) for a complete discussion of reasons for subject study withdrawal.

Discontinuation information [e.g., date and the reason(s) for discontinuation] will be recorded in the Subject's Case Report Form (CRF). Subjects who discontinue prematurely should complete the Week 6 assessment procedures within 2 days following their last transcranial magnetic stimulation (TMS) treatment session. See the Schedule of Events for the specific procedures to be performed at this discontinuation visit.

Subjects withdrawn from the study due to an AE will be followed up for 30 days or until resolution. Subjects withdrawn from the study will not be replaced, regardless of the reason for withdrawal. An effort will be made to determine why a subject does not return for the required visits or is dropped from the study. This information will subsequently be recorded on the subject's CRF.

Subjects will be encouraged to remain compliant with all expected study visits. Non-adherence to expected study visits will be documented and may result in removal from the study. This will be clearly discussed during the consent/assent process and reinforced throughout the study through regular screening for issues with compliance.

[name] will assist with clinical referral for all subjects who voluntarily withdraw from the study or are withdrawn by the research team and PI. Specifically, [name] will offer ongoing clinical care or community referrals based on the preference of the subject.

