If a seizure occurs during the study, TMS (aTBS) treatment as part of the study will be discontinued. Ongoing monitoring of mood and neurocognitive symptoms per the study protocol will be offered. Any seizure will be reported to the Mayo Clinic IRB, Data and Safety Monitoring Board (DSMB), the FDA and MagVenture as required per agreements, regulations, and policies.

Cardiogenic syncope (fainting) is another related but rare risk. In the event of fainting, the study team members will ensure that the subject is not injured by falling out of the TMS chair (which would be unlikely). The PI ([name]) or covering study physician will assess the subject immediately and take further action as clinically appropriate. The PI will consult with the subject, subject's parent or guardian, and the subject's primary care physician regarding next steps which may include exit from the study.

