## 1.6 Anticipated Duration of the Clinical Investigation

The interventional component of the study involves 30 sessions of aTBS over 2 weeks. The research team will then follow adolescents subjects assigned to both study arms (active and sham) for 1 year. Hence, the duration of participation is approximately 13 months.

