##### **4.4.2 Data Collection and Follow-up for Withdrawn Subjects**

In the event that a subject has withdrawn from the treatment phase of the study, the research team will attempt to obtain permission for data collection for the twelvemonth follow-up period.

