## 6 Study Procedures

**Experimental Design:** This is a randomized, double-blind, sham-controlled trial of sequential bilateral aTBS in adolescents with depression and suicidal ideation (Figure 7). Three sessions are administered daily for 10 days (5 days per week). During each session, cTBS in which 1800 pulses are delivered continuously over 120 seconds to the right dorsolateral prefrontal cortex (RDPFC) is administered first, followed by iTBS in which 1800 pulses are delivered in 2 second bursts, repeated every 10 seconds for 570 seconds (1800 pulses) to the left dorsolateral prefrontal cortex (LDPFC). The TBS parameters were adopted from prior work, with 3-pulse 50 Hz bursts given every 200 ms (at 5 Hz) with an intensity of 80% of active MT. The comparison group will receive 3 daily session of bilateral sham TBS treatment for 10 days.

All subjects will receive standard of care treatment for depression and suicidal ideation including daily psychotherapeutic skill sessions (Figure 8). The 10-day psychotherapy treatment program was adapted from recent work and input from a consultant ([name]). The primary outcome measure is suicidal ideation assessed with the C-SSRS severity of ideation subscale. Depressive symptom severity will be assessed with the CDRS-R.

| Table 3. Schedule of Events                                                                                                   |                  |                 |                                              |                                                |                                 |                                                 |
|--------------------------------------------------------------------------------------------------------------------------------------|------------------|-----------------|----------------------------------------------|------------------------------------------------|---------------------------------|-------------------------------------------------|
| Study Activity                                                                                                                | Screening | Baseline | Daily aTBS and psychotherapy sessions | Posttreatment (End of 10-day treatment) | Monthly Follow-up Visits | Comments                                 |

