**Clinical and Standardized Assessments:** At screening subjects will undergo a urine drug screen, urine pregnancy test, MINI-Kid or MINI interview, Brief Affective Neuroscience Personality Scale, CDRS-R, C-SSRS, Childhood Trauma Questionnaire, Clinical Global Impressions Scale (CGI), Safety Screening for TMS, Young Mania Rating Scale, Adverse Event Rating Scales, Medical History, Physical Exam, Vital Signs, Pubertal Development Scale, and the Beck Depression Inventory-II (BDI-II). At the baseline visit subjects will repeat the CDRS-R, C-SSRS, CGI, BDI-II, and Adverse Rating Scales. Other baseline assessments include the NIH Toolbox Cognition Battery, Auditory Threshold Testing, and a Pre-treatment Expectation and Experience Questionnaire. Subjects will undergo TMS-EMG testing and TMS-EEG testing at the baseline line visit. The C-SSRS (suicidal ideation severity subscale, which is the primary outcome measure) will be assessed daily for the 10 treatment days. The CDRS-R, CGI, and BDI-II will be collected weekly during the treat period (baseline, after 5 treatments, and posttreatment). After the final day of treatment, the subjects will complete the C-SSRS, CDRS-R, CGI, BDI-II, Post-treatment Expectation and Experience Questionnaire and the NIH Toolbox Cognition Battery. Vital signs will be collected at this posttreatment visit. Subjects will undergo posttreatment TMS-EMG and TMS-EEG testing. Follow-up, post-treatment assessments will be collected each month over the 12-month follow-up period. These monthly assessments will include the C-SSRS, CDRS-R, CGI, BDI-II, number of hospitalizations related to suicidality, and number of emergency department visits

related to suicidality. Concurrent medications, concurrent psychotherapy, and adverse events will be collected at every study visit.

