##### ***Subject Stopping Rules***

Subjects may withdraw voluntarily from the study at any time. The subject stopping rules apply to the two-week period when the subjects are receiving the study intervention. (active or sham sequential bilateral aTBS). These rules do not apply to subjects in the naturalistic 1-year follow-up portion of the study. Subjects will be withdrawn (please refer to section 4.4) from the study by the PI/Sponsor if a subject:

- experiences a seizure,
- experiences a DSM-5-confirmed treatment-induced mania,
- experiences psychotic symptoms
- is non-compliant with study procedures; or
- endorsed illicit drug use or has a positive urine drug screen during the study

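### Early stoppers are sent to a Week 6 visit that Table 3 does not list, the rules on leaving the study conflict, and nothing says whether the daily C-SSRS continues to day 10

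*Protocol*

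**What the plan says.** On the visit, Section 4.4.1 says: "Subjects who discontinue prematurely should complete the Week 6 assessment procedures within 2 days following their last transcranial magnetic stimulation (TMS) treatment session". It then directs staff elsewhere for the content: "See the Schedule of Events for the specific procedures to be performed at this discontinuation visit". Section 1.6 gives the length of treatment: "The interventional component of the study involves 30 sessions of aTBS over 2 weeks". Table 3 in Section 6 has five timing columns: screening, baseline, daily sessions, one headed "Posttreatment (End of 10-day treatment", and monthly follow-up. Section 6.4 says that the C-SSRS ideation severity subscale, the primary outcome, "will be assessed daily for the 10 treatment days".

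On the consequence of stopping, the protocol speaks in several places:

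- Section 8.5, Subject Stopping Rules: "Subjects will be withdrawn (please refer to section 4.4) from the study by the PI/Sponsor if a subject" has a seizure, confirmed treatment-induced mania, psychotic symptoms, non-compliance, or drug use. These rules are confined to the two treatment weeks.
- Table 4, YMRS entry: full-criteria mania or hypomania ends study participation, with clinical follow-up.
- Section 1.5.2, seizure: the stimulation is discontinued, and "Ongoing monitoring of mood and neurocognitive symptoms per the study protocol will be offered".
- Section 4.4.2: for a subject who leaves the treatment phase, "the research team will attempt to obtain permission for data collection for the twelvemonth follow-up period".
- Section 8, pregnancy detected during treatment: no more stimulation, but 12-month follow-up continues.

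On analysis, Section 7.3 includes every randomised subject with at least one device exposure. The Study Summary treats missing data in the primary GEE as missing at random. The sensitivity analysis in Section 7.2 describes models for non-random missingness, to be built only if they are judged to be needed.

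**The concern.** A rule that staff must follow within two days of the last session refers to a visit that the schedule does not list. Two people could reasonably carry out different assessments for the same subject.

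The more consequential gap concerns the primary outcome. The 8.5 rules operate in the same two weeks in which the daily C-SSRS is collected. If they are read as ending study participation, the remaining acute scores are not collected. If the seizure or pregnancy wording is taken as the model, some observation continues, but neither passage mentions the daily C-SSRS. Section 4.4.2 covers only the 12-month period and leaves the remaining acute days unaddressed.

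The subjects concerned belong to the all-treated population, and their exits come after randomisation. Several of the listed reasons could be related to the treatment arm or to clinical course. Scores that were never collected cannot be recovered by a later analysis plan, so the matter belongs in the protocol.

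**Working it through.** **1. Is there a Week 6 visit?** Treatment takes 2 weeks, and none of the five timing columns of Table 3 is labelled Week 6, discontinuation or early termination. The nearest match for a contact within two days of the last session is the Posttreatment column, which includes the C-SSRS. By the calendar, the first monthly visit would fall about 2 + 4 = 6 weeks after baseline, but the protocol never gives it that label. The two columns differ: Posttreatment also has cognition, audiometry, vital signs and TMS neurophysiology. The protocol does not say which of these items apply to someone who stopped early, for example because of a seizure.

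**2. Do the stopping passages agree?** Section 8.5 and the YMRS entry of Table 4 end study participation. The seizure text, Section 4.4.2 and the pregnancy rule stop treatment and retain, offer or seek further observation. Seizure falls under both kinds of rule. Section 4.4.1 says that missing visits may lead to removal, while 8.5 makes withdrawal for non-compliance mandatory. Sections 4.4 and 8.5 refer to each other without settling the matter.

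**3. The plan's own sample size.** Inputs from Section 7.1: odds ratio 2.85, sham proportion 0.50, 10 measurements, within-subject correlation 0.50, two-sided alpha 0.05, power 80%.

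- Second proportion: 2.85 / (1 + 2.85) = 0.740.
- Single-measurement two-proportion size (pooled): 63 per group.
- Repeated-measures factor: (1 + 9 × 0.5) / 10 = 0.55.
- 63 × 0.55 = 34.65, so 35 per group, as stated.
- 70 / 0.9 = 77.8, so 78, consistent with about 80.

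**4. Cost in power.** A subject with k daily scores contributes k / (1 + (k − 1) × 0.5) effective observations: 10 / 5.5 = 1.818 for k = 10, and 1 for k = 1. With 40 per arm and complete data, the effective number per arm is 40 × 1.818 = 72.7 and power is 0.855. In an assumed unfavourable case of 5 stoppers per arm with one score each, it is 35 × 1.818 + 5 = 68.6 and power is 0.834. Across 2 to 5 stoppers per arm keeping 1 to 8 scores, power runs from 0.834 to 0.855. On the log-odds-ratio calculation the corresponding figures are 0.816 and 0.838.

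**5. Possible bias (illustration only).** Assume no true effect, 40 per arm, a favourable-outcome rate of 0.50 in both arms, and s stoppers in the active arm only, with favourable rate q, whose outcomes are ignored. The observed active rate is (20 − q × s) / (40 − s), and the apparent odds ratio is that rate's odds divided by 1.

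| s | q | observed rate | apparent OR |
|---|---|---|---|
| 1 | 0.25 | 0.506 | 1.03 |
| 2 | 0 | 0.526 | 1.11 |
| 4 | 0.25 | 0.528 | 1.12 |
| 4 | 0 | 0.556 | 1.25 |
| 5 | 0 | 0.571 | 1.33 |

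The values of s and q are assumptions, and stopping on one side only is the unfavourable case. The calculation uses a single binary status, whereas the primary analysis is an ordinal GEE over 10 days.

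**The case against.** The strongest reply is that this is mostly a wrong label. A discontinuation assessment within two days is plainly intended, Posttreatment is the natural column for it, and it includes the C-SSRS. Scores before stopping remain in the analysis, so only the remaining acute days are at issue. This stands as a limit on the size of the problem. It does not settle which items apply, or whether scores are sought up to day 10.

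A reader might infer more than the text supports:

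- *That early stoppers leave the study rather than the stimulation.* This takes one side of a contradiction as the rule. Sections 1.5.2, 4.4.2 and 8 separate the two.
- *That the daily C-SSRS ends with stimulation and is lost selectively.* The protocol is silent on this, and no stopping rate by arm or reason is given. Selective loss is a risk that has not been shown.
- *That two missed treatment days trigger withdrawal.* Section 5.4 only defines non-adherence to the treatment regimen. No passage ties that threshold to 8.5, which uses a different phrase.
- *That 10% dropout could move an arm by 10 points.* With 4 of 40 missing, 10 points is the full width from best to worst case. The largest shift from the observed proportion is 0.10 × 0.50 = 5 points at 0.50 and 0.10 × 0.74 = 7.4 points at 0.74, and only if all the missing subjects had the same outcome.
- *That the analysis has no answer to non-random dropout.* Section 7.2 names dropout, shared-parameter and pattern-mixture models. The fair criticism is that they are conditional and depend on untestable assumptions where scores could have been collected.

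It can also be said that the 8.5 rules were developed with the FDA, and that continuing assessments after mania or psychotic symptoms involves clinical judgement. That stands, and the fix allows for it.

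**Conclusion.** The point holds in three parts. The reference to Week 6 leads to nothing in Table 3. The passages on what follows early stopping contradict one another and must be reconciled. No passage says whether the primary outcome is still collected to day 10. The first two are plain on the page; the third is a silence that matters because the analysis population includes everyone treated.

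The effect on power is small, at most about 2 points under the assumed patterns. The issue is possible bias, and its size cannot be computed from the protocol. The apparent odds ratios of 1.03 to 1.33 depend on assumed one-sided, outcome-related stopping by 1 to 5 of 40 subjects, and they indicate scale only. Missing at random is assumed in the primary model, and the alternatives are optional, so collecting the scores is the better protection. The correction should be made, but the documents do not establish that the trial's result would be distorted.

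**What to change.** 1. In Section 4.4.1, replace the Week 6 reference with the Posttreatment procedures of Table 3, and have the sponsor state which items apply to subjects who stop early.
2. Reconcile Sections 1.5.2, 4.4, 8 and 8.5 and the YMRS entry of Table 4 under one definition that separates stopping stimulation from leaving the study. Which clinical events lead to which outcome is for the sponsor to settle, and the stopping criteria are left as they are.
3. State that subjects who stop stimulation but have not withdrawn consent for assessments are still asked for the scheduled C-SSRS to day 10, the posttreatment visit and monthly follow-up, where the sponsor judges this clinically appropriate.

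The cost is a short amendment, possibly with notice to the FDA and the DSMB because the 8.5 rules were developed with the FDA. The extra work is assessments that are already scheduled, for up to about 8 participants (10% of 80). Those who withdraw consent for assessments would still be missing.

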| Young Mania Rating Scale (YMRS)                                                                                                      | X                | X               | X                                            | X                                              | X                               | Collected weekly during 10-day treatment period |
| Childhood Depression Rating Scale – Revised (CDRS-R)                                                                                 | X                | X               | X                                            | X                                              | X                               | Collected weekly during 10 day treatment period |
| Columbia Suicide Severity Rating Scale (C-SSRS)                                                                                      | X                | X               | X                                            | X                                              | X                               | Collected daily during 10 day treatment period  |
| Childhood Trauma Questionnaire                                                                                                       | X                |                 |                                              |                                                |                                 |                                                 |
| Beck Depression Inventory-II (BDI-II)                                                                                                | X                | X               |                                              | X                                              | X                               | Collected weekly during 10 day treatment period |

|                                                                                      |   |   |   |   |   |                                                 |
|--------------------------------------------------------------------------------------|---|---|---|---|---|-------------------------------------------------|
| Pre/Post Treatment Expectations and Experience Questionnaire (Adolescent and Parent) |   | X |   | X |   |                                                 |
| Clinical Global Impressions Severity Scale (CGI-S)                                   | X | X | X | X | X | Collected weekly during 10 day treatment period |

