| YMRS-Young Mania Rating Scale                                                        | This is an 11-item measure used to assess for manic symptoms. The YMRS scale will be completed at baseline and repeated during the course of study participation if symptoms of mania occur in a study subject. If the YMRS is positive, A MINI/MINI-Kid will be repeated to evaluate for mania. If the study subject meets full DSM-5 criteria for mania or hypomania he or she will be discontinued from the study and followed clinically.                                                                                                                                                                                                                                                                                                                                                                                                                                                                                                                                                                                                |
| TMS Neurophysiology Measures                                                         | TMS-EMG (LICI-100) and TMS-EEG (LICI-100 and N100) neurophysiology measures will be collected in adolescent subjects at baseline and after the final day of sequential bilateral aTBS.
25, 81                                                                                                                                                                                                                                                                                                                                                                                                                                                                                                                                                                                                                                                                                                                                                                                                                                                           |

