### **Post-study Adverse Event**

All unresolved adverse events should be followed by the investigator until the events are resolved, the subject is lost to follow-up, or the adverse event is otherwise explained. The study team will report unresolved adverse events to the DSMB when the subject exits the study. The study team will track adverse events through resolution and report to the DSMB as feasible (if the patient can be contacted or monitored). The study team will report unresolved adverse events that cannot be tracked through resolution to the DSMB (the subject cannot be contacted or is unwilling to have contact with the study team). At the last scheduled visit, the study team will instruct each subject to report, to the local investigator, any subsequent event(s) that the subject, or the subject's personal physician, believes might reasonably be related to participation in this study. The local investigator should notify the study regulatory sponsor of any death or adverse event occurring at any time after a subject has discontinued or terminated study participation that may reasonably be related to this study. The sponsor should also be notified if the local investigator should become aware of the development of problems, cancer or of a congenital anomaly in a subsequently conceived offspring of a subject that has participated in this study.

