### **8.2 Recording of Adverse Events**

At each contact with the subject, the investigator must seek information on adverse events by specific questioning and, as appropriate, by examination. Study subjects will be routinely questioned about adverse effects at study visits. Information on all adverse events should be recorded immediately in the source document, and also in the appropriate adverse event section of the case report form (CRF) or in a separate adverse event worksheet. All clearly related signs, symptoms, and abnormal diagnostic, laboratory or procedure results should be recorded in the source document.

All adverse events occurring during the study period must be recorded. All observed or volunteered adverse effects (serious or non-serious) and abnormal test findings, regardless of the treatment group if applicable or suspected causal relationship to the investigational device or if applicable other study treatment or diagnostic product(s) will be recorded in the subjects' case history. For all adverse effects sufficient information will be pursued and/or obtained as to permit; an adequate determination of the outcome, an assessment of the causal relationship between the adverse effect and the investigational device or, if applicable other study treatment or diagnostic product. The clinical course of each event should be followed until resolution, stabilization, or until it has been ultimately determined that the study treatment or participation is not the probable cause. Serious adverse events that are still ongoing at the end of the study period must be followed up, to determine the final outcome. Any serious adverse event that occurs after the study period and is considered to be at least possibly related to the study treatment or study participation should be recorded and reported immediately.

A form should be created for capturing information related to adverse events and submitted with the IDE application to the FDA.

Recommended information to capture on the Adverse Event CRF:

- Subject Study Number/Identifier
- Device information (model and serial number)
- Date of event onset
- Description of the event
- Indication if study treatment was discontinued, or if investigational device was removed
- Subject current status, or if the event was resolved

- Principal Investigator assessment of if the event was serious and justification for determination
- Principal Investigator assessment of causality and relationship to study treatment.

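### Table 4 removes subjects with mania or hypomania from the study at any time, which contradicts section 8.5 and leaves follow-up-year removals with no provision for later data

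*Protocol*

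**What the plan says.** Rules on removal:

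- **Section 6.4, Table 4, YMRS entry.** The scale is completed at baseline and "repeated during the course of study participation if symptoms of mania occur in a study subject". A positive score leads to a repeat diagnostic interview. If mania or hypomania is confirmed, "he or she will be discontinued from the study and followed clinically". No time limit is given.
- **Section 6, Table 3.** The YMRS is marked at screening, baseline, during treatment, post-treatment and at the monthly follow-up visits.
- **Section 8.5, Subject Stopping Rules.** The list opens with "Subjects will be withdrawn (please refer to section 4.4) from the study by the PI/Sponsor if a subject". It names seizure, confirmed treatment-induced mania, psychotic symptoms, non-compliance and illicit drug use. Hypomania is not on it. On scope, the section says: "These rules do not apply to subjects in the naturalistic 1-year follow-up portion of the study".
- **Section 4.4.1** sends the reader to section 8.5 for the full account of withdrawal reasons.

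Rules on data after removal:

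- **Section 4.4.2.** For a subject withdrawn from the treatment phase, the team tries to get permission to collect the 12-month data.
- **Section 8, pregnancy paragraph.** A pregnancy found during treatment stops stimulation, and the subject stays in the 12-month follow-up.
- **Section 1.5.2.** After a seizure, stimulation stops and protocol monitoring is offered. Verified mania is an SAE and is tracked with the YMRS.

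Rules on how long an adverse event is followed:

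- **Section 4.4.1:** "Subjects withdrawn from the study due to an AE will be followed up for 30 days or until resolution".
- **Section 8.1:** "All unresolved adverse events should be followed by the investigator until the events are resolved".
- **Section 8.2:** "The clinical course of each event should be followed until resolution, stabilization, or until it has been ultimately determined".

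**The concern.** The assessment table and the stopping-rules section give different answers to the same question: does mania or hypomania end a subject's participation? They differ on which events count and on when the rule applies. The difference matters most in the follow-up year, because the one provision for keeping data on withdrawn subjects is written for the treatment phase only.

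Suicidality-related emergency visits and hospitalizations over 12 months are a primary safety endpoint (section 3.4) and the Hypothesis 1c outcome. Monthly C-SSRS scores are the Hypothesis 1b outcome. Anyone who received one stimulation session is in the all-treated population (section 7.3), so months not collected after removal become missing data for a subject who remains in the analysis. The removal would follow a psychiatric event that may be device-related, so the missingness could be linked to both arm and outcome.

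**Working it through.** No design figure is at issue, so the check is mainly a comparison of text.

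**Step 1. Compare the two rules.**

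| | Table 4, YMRS entry | Section 8.5 |
|---|---|---|
| Mania | Yes | Yes, if DSM-5 confirmed and treatment-induced |
| Hypomania | Yes | Not listed |
| Two treatment weeks | Applies | Applies |
| 12-month follow-up | No limit stated, so applies | Expressly excluded |

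**Step 2. Run four cases through the rules.**

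- *Mania during treatment.* Both rules remove the subject. Section 4.4.2 then applies, and 12-month data are sought.
- *Hypomania during treatment.* Table 4 removes the subject and section 8.5 does not. If the subject is removed, section 4.4.2 still applies.
- *Mania during follow-up.* Table 4 removes the subject. Section 8.5 does not apply. Section 4.4.2 does not reach this subject.
- *Hypomania during follow-up.* As for mania during follow-up, except that section 8.5 would not list the event in any case.

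The last two cases are the gap.

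**Step 3. Could Table 4 mean stopping stimulation only?** That reading is possible during the treatment weeks. It is not possible in the follow-up year, when there is no stimulation left to stop. The instruction would then either end follow-up or have no effect. The phrase about clinical follow-up points to care outside the study schedule.

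**Step 4. Can the rule be triggered in follow-up?** Yes. Table 3 marks the YMRS at monthly visits. The narrative list of monthly assessments in section 6.4 does not name the YMRS, but Table 4 triggers it on symptoms at any point in participation, so the rule can operate either way.

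**Step 5. Scale for one subject.** Assume 80 subjects, 40 per arm under 1:1 allocation, and 12 monthly visits each. The section 12.3 stipend agrees with 12 visits: 50 + 10 × 10 + 50 + 10 × 12 = 320.

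- Planned monthly visits: 80 × 12 = 960 in total, and 40 × 12 = 480 per arm.
- A subject removed at the month *m* visit loses 12 − *m* later visits. As an illustration, *m* = 4 loses 8: 8/960 = 0.83% overall, or 8/480 = 1.67% of one arm.
- The most that one subject can lose is all 12 visits: 12/960 = 1.25% overall, or 12/480 = 2.5% of one arm.
- For a stop in the treatment phase, the loss is 0 if permission under section 4.4.2 is given.

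These figures give the share of one subject. They do not say how often this would happen, because the protocol gives no rate for these events.

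**Step 6. Length of adverse-event follow-up.** Section 4.4.1 gives two limits and does not say which governs. Sections 8.1 and 8.2 follow events to resolution or another defined end, with no day limit. If the later limit governs, the three sections agree.

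**The case against.** The best answer is that section 4.4.1 names section 8.5 as the complete statement of withdrawal reasons. A table describing assessments should not be read as adding one, so section 8.5 would prevail and a subject with mania in follow-up would stay in. This is a sensible way to settle the conflict, but the protocol does not say that section 8.5 overrides Table 4. Site staff acting on a positive YMRS would be following a direct instruction in the table. The contradiction stands, and correcting it is a short edit.

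A reader might also infer that every subject stopped for seizure, mania or psychotic symptoms is lost to the 12-month follow-up. The text does not support that. Section 8.5 operates only in the treatment weeks, so each of its withdrawals falls under section 4.4.2, which seeks the 12-month data. After a seizure, section 1.5.2 also offers continued protocol monitoring. Compared with the pregnancy rule, the difference is one of default: retained unless declined, against retained if permission is obtained.

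A third inference would be that section 4.4.1 cuts off adverse-event follow-up at 30 days. Sections 8.1 and 8.2 both point the other way, section 8.2 requires ongoing SAEs to be followed to final outcome, and section 1.5.2 classes verified mania as an SAE. The wording can be read consistently with those sections, so it is an editorial matter.

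Finally, section 7.2 plans a missing-at-random analysis with not-at-random sensitivity models. That helps in part, but those models are conditional on being judged necessary, and collecting the data is preferable to modeling their absence.

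**Conclusion.** The point holds as a minor inconsistency. Table 4 and section 8.5 disagree on hypomania and on the follow-up year, and section 4.4.2 does not cover a subject removed during follow-up. Followed as written, Table 4 would take such a subject out of the primary safety endpoint and the Hypothesis 1b and 1c outcomes from that date, with no provision to continue collection.

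The effect is probably small. One affected subject accounts for at most 1.25% of planned monthly visits, or 2.5% of one arm, assuming 80 subjects split equally and 12 visits each. A reader might go further and conclude that the 12-month comparison will be biased. The documents do not support that: they give no event rate and no basis for a difference between arms, so neither the size nor the direction of any bias can be determined. Sample size, power and the 10-day primary analysis are not affected.

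**What to change.** 1. In Table 4 (YMRS) and section 8.5, state that mania or hypomania during the treatment weeks ends stimulation only, and that the subject stays in the 12-month follow-up unless the subject or guardian declines. Apply the same wording to seizure and psychotic symptoms. Section 8 already does this for pregnancy.
2. In Table 4, state that mania or hypomania arising in the follow-up year does not end follow-up.
3. Make the two lists agree on whether hypomania is a reason to stop.
4. As an editorial change in section 4.4.1, add that the later of the two limits applies, so that it matches sections 8.1 and 8.2.

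The cost is a few sentences and monthly visits for a few extra subjects. For treatment-phase stops the gain is small, because section 4.4.2 already attempts to obtain the data. The main gain is for events that arise during follow-up.
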